### Patient registration requirements

Participants are recruited by clinical research coordinators at participating sites, including the main member and NCI Community Oncology Research Program (NCORP) network sites of the Alliance for Clinical Trials in Oncology. Local site coordinators complete informed consent procedures, assess the need for a study-provided smartphone, and collect study-required contact information for intervention administration. Following consent, site coordinators complete registration and randomization procedures via a web-based registration system, which accounts for the stratification factors: age and self-identified race. Participants are randomized in a 1:1:1:1 ratio to participate in one of the four study arms. Randomization is stratified on the basis of age, in years (< 50; ≥ 50), and race (Black women; non-Black women). Participants return to the clinic for a required, in-person baseline visit to set up the Patient Cloud (ePRO) and Pillsy smartphone applications and receive other arm-specific resources. The schedule of enrollment, interventions, and assessment can be found in Fig. 1.

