### Sample size

Enhanced usual care adherence at 12 months is assumed to be 69%, based on our preliminary studies of pharmacy refill data from claims in Medicare, Medicaid, and private insurance populations, using weighted estimates of 12-month adherence among Black women < 50 years old, non-Black women < 50 years old, Black women ≥ 50 years old, and non-Black women ≥ 50 years old. We hypothesize 81% adherence for the TMR-only and MI-only intervention arms based on preliminary data from the GETSET MI counseling pilot intervention [37, 45]. To maintain a primary family-wise two-sided type I error rate of* α* = 0.05, the two chi-square tests will be conducted with nominal *α* = 0.025. At a 2.5% two-sided significance level, the study will have at least 80% power to detect differences in adherence (81% in single component intervention arms vs 69% in enhanced usual care) if 263 evaluable patients are randomized each to the TMR-only, MI-only, and enhanced usual care arms. Because we anticipate ineligible and loss to follow-up of approximately 11%, consistent with other clinical trials of cancer survivors, we will over-recruit, rendering a recruitment target of 1180 randomized patients total (295 per arm). Power Analysis and Sample Size (PASS) software (PASS v15, NCSS, Kaysville, UT) was used to conduct the power analysis.

Young age and self-reported Black race have been shown to be risk factors for low ET adherence [13, 19, 20]. As such, the study is designed to accrue 30% (or 354 of 1180) of patients who self-identify as Black as well as 30% who are < 50 years old at time of recruitment. Additionally, the ideal case is for race and age to be uncorrelated with one another so that they have independent effects on the outcome of interest. To achieve this, we have defined distinct accrual targets for four non-overlapping groups (i.e., Black women < 50 years old, non-Black women < 50 years old, Black women ≥ 50 years old, and non-Black women ≥ 50 years old) and close accrual for each group independently. The target accrual numbers for each group are shown in Table 2.

**Table 2 Tab2:** Accrual targets by race and age strata

Age (years)	Black	Non-Black	Total
< 50	106	248	354
≥ 50	248	578	826
Total	354	826	1180

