
## Outcomes

### Primary endpoint

The primary endpoint is ET adherence at 12 months post-randomization as measured by electronic pill monitoring cap (Pillsy-reported). Patients will be labeled as adherent if the proportion of days covered by any ET medication is at or above 80% (i.e., taking ET at least 292 of 365 days). Women who do not take ET for at least 292 days will be deemed non-adherent at 12 months. The primary analysis will be based on a modified intention-to-treat population (mITT), defined as all women who signed a consent form, met the eligibility criteria, were randomized, and took ET on at least one occasion; furthermore, these women will be analyzed in the arms to which they were randomized. For the primary analysis, two comparisons will be made using two chi-squared tests: TMR-only versus enhanced usual care and MI-only versus enhanced usual care. For each comparison, statistical significance will be assessed at the 2.5% level. Should either TMR-only or MI-only arms achieve statistical significance at its allocated α-level (or accumulated unused α-levels if both achieve statistical significance), then the TMR + MI vs enhanced usual care comparison will be assessed and the unused α-level passed down and applied to determine statistical significance. In this way, the type I error rate applied to the primary family of endpoints can be controlled at the 5% level.

As a sensitivity analysis, we will assess if the intervention effects on ET adherence differ by the stratification factors of age and race. Therefore, logistic regression is planned to model the binary measure of adherence at 12 months separately for each intervention vs enhanced usual care comparison so that three separate logistic regression models will be estimated. Covariates included in each logistic regression model will be age (< 50 years; ≥ 50 year), race (Black women; non-Black women), intervention arm assignment, and the interaction terms between each stratification factor (age and race) and intervention arm assignment to ascertain whether the magnitude of the intervention effect is different across the levels of age and race. Statistical significance of the interaction terms will be assessed at the 10% level with the likelihood ratio test comparing models with and without the interaction terms.

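### The valid gatekeeping rule could be improved within its own 5% budget by returning alpha from TMR + MI to a single-component comparison not yet rejected

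*Protocol article*

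**What the plan says.** Under Sample size, the error budget is set as follows: "To maintain a primary family-wise two-sided type I error rate of" 0.05, the two single-component chi-square tests are each run at 0.025. The power statement covers those two tests only: "At a 2.5% two-sided significance level, the study will have at least 80% power to detect differences in adherence". The alternative is 81% in each single arm against 69% under control, and the condition reads "if 263 evaluable patients are randomized each to the TMR-only, MI-only, and enhanced usual care arms". No adherence rate is given for the combination arm.

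Under Primary endpoint, the TMR + MI comparison is opened by a significant result in either single arm. Then "the TMR + MI vs enhanced usual care comparison will be assessed and the unused α-level passed down and applied to determine statistical significance". The level for TMR + MI is therefore 2.5% if one single arm has succeeded and the accumulated 5% if both have. The sequence stops there, with the statement that the primary family is controlled at 5%.

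**The concern.** Alpha travels one way, from the single arms to the combination. Suppose TMR-only is significant at 2.5%, TMR + MI is then significant at the passed-on 2.5%, and MI-only has a p-value between 0.025 and 0.05. Under the rule as written, MI-only is not declared effective. Yet both hypotheses that consumed alpha have been rejected, so the whole 5% is free to be used on MI-only. A Bonferroni-based graphical procedure would allow that test at 5%. The same applies with the two components exchanged.

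At stake is the power to establish the second component. Showing which components work is the purpose of the two primary comparisons.

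**Working it through.** **Inputs from the article.** Control adherence 69%, single arms 81% each, two-sided alpha 0.025 per comparison, 263 evaluable per arm, 1:1:1:1 allocation. **Assumed, because not stated:** TMR + MI adherence, varied from 69% to 85%, and a weaker single arm at 77%.

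**1. The plan's own figure.** The difference is 0.12, the mean rate 0.75, z(0.9875) = 2.2414 and z(0.80) = 0.8416.

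n = [2.2414·√(2·0.75·0.25) + 0.8416·√(0.69·0.31 + 0.81·0.19)]² / 0.12² = (1.8830)² / 0.0144 = 246.2, that is 247 per arm.

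With the continuity correction: (246.2/4)·[1 + √(1 + 4/(246.2·0.12))]² = 262.6, that is 263. The stated number reproduces. With 263 per arm, uncorrected power is 82.8% at alpha 0.025, so the claim of at least 80% holds without any recycling.

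**2. Ceiling on the gain.** At 263 per arm and 81% against 69%, power at alpha 0.05 is 89.1%. A return step therefore cannot add more than 89.1 − 82.8 = 6.3 points to a single arm at the design alternative. It adds less in practice, because the other single arm and TMR + MI must be rejected first.

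**3. Validity of the return step.** Initial weights are 0.025, 0.025 and 0 for TMR-only, MI-only and TMR + MI. Each single arm passes weight 1 to TMR + MI, and TMR + MI passes weight 1/2 to each single arm. Once TMR-only is rejected, the standard update makes the edge from TMR + MI to MI-only (1/2 + 0)/(1 − 1/2·1) = 1. If TMR + MI is then rejected at 0.025, MI-only is tested at 0.025 + 0.025 = 0.05. This is a closed testing procedure with family-wise level 5%. Every rejection under the current rule is kept, and the test of TMR + MI is unaffected.

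**4. Size, by simulation** (600,000 trials per scenario, 263 per arm, shared control at 69%, two-sided pooled tests). Entries are power under the current rule → with the return step; repeat runs differ by about 0.1 point.

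| TMR / MI / TMR + MI | Single arm | Both single arms |
|---|---|---|
| 81 / 81 / 81 | 83.1% → 86.2% | 73.1% → 79.3% |
| 81 / 81 / 85 | 83.1% → 87.2% | 73.1% → 81.4% |
| 81 / 81 / 78 | gain 1.5 points | gain 3.1 points |
| 81 / 81 / 69 | gain 0.1 point | gain 0.1 point |
| 81 / 77 / 83 | weaker arm 43.3% → 52.8% | – |

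The path on which the step can act (exactly one single arm plus TMR + MI rejected) occurs in about 14% of trials at 81/81/81, 19% at 81/81/85 and 42% at 81/77/83.

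**5. Error rates.**
- Global null: family-wise error is 4.7% under both rules. This is uninformative about the change, because the first rejection alone determines it.
- One single arm null, the other at 81%, TMR + MI at 85%: 2.5% under the current rule, 4.4% with the return step.
- One single arm null, the other two at 95%: 2.5% becomes 5.1%. The excess over 5.0% reflects the binomial approximation of the chi-square test, not the procedure.
- The current rule itself gives 2.5% to 5.0% across the null configurations tried.

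**The case against.** The strongest reply is that nothing in the plan is wrong. The scheme controls the family-wise error as claimed, the power promise is made at 2.5% and is met, and choosing among valid gatekeeping procedures is a matter of preference. That stands. A reader might infer that the trial is underpowered or its error control flawed; the reproduced sample size and the simulated error rates contradict both.

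A reader might also infer a fixed loss of 4 to 9 points. The documents do not support that. They state "We hypothesize 81% adherence for the TMR-only and MI-only intervention arms" and give no rate for the combination. At the stated single-arm rates the gain falls below 4 points unless TMR + MI does better than one component. About 9 points needs a weaker second arm, which departs from the stated hypothesis, together with an effective combination.

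A third tempting reading is that the step is free in terms of type I error. Only the 5% ceiling is preserved. For one ineffective component alongside two real effects, the false-positive chance can roughly double.

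Finally, the article condenses a fuller protocol and the analysis plan is not shown, so a return step could exist there. The article does, however, set out its sequence from the first tests to the claim of 5% control, and the criticism is of that rule as written. The late timing is also fair: the article reports 1024 of 1180 patients accrued by 15 September 2023, interim results go to the DSMB, and amendments need several approvals. These are costs to weigh; they do not refute the point.

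**Conclusion.** The point holds as a modest, optional improvement to a valid procedure. Within the plan's own 5% budget, a return step raises power for each single-component comparison by about 3 points at 81/81/81 and 4 at 81/81/85. It raises the chance of showing both components from 73% to 79–81% and leaves TMR + MI power unchanged. A weaker arm at about 77% can gain about 9 points if the combination works (83% assumed). If TMR + MI has no effect, the gain is essentially nil. All of these sizes rest on 263 evaluable per arm, 69% control adherence and combination rates that the article does not give.

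Against this stands a rise from 2.5% to at most about 5% in the chance of falsely rejecting one null single arm when the other two effects are real.

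**What to change.** Before outcome data are seen, add one sentence to the primary analysis: *If one single-component comparison and then TMR + MI versus enhanced usual care are significant, the alpha passes to the remaining single-component comparison, which is then tested at two-sided 0.05.* Show the graph in the analysis plan: each single arm to TMR + MI with weight 1, and TMR + MI to each single arm with weight 1/2, becoming weight 1 to the remaining arm once the other is rejected.

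The return must go through TMR + MI. Passing alpha directly between the single arms first would cost the combination 6.7 points of power at 81/81/81 and 11.1 at 81/81/85.

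The cost is a protocol amendment with its approvals (Alliance Cancer Control Program, NCORP and the NCI CIRB), plus a plain statement of the higher false-positive chance for a single null component. No extra patients or data are needed. If the sponsor prefers to keep the sequence ending at TMR + MI, a sentence giving the reason would suffice.

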### Exploratory endpoints

In addition to the primary endpoint, we will observe 13 exploratory endpoints. These include self-reported adherence, patient-reported MUSE score, PROMIS physical health subscale score, PROMIS mental health subscale score, PROMIS depression short form, Concerns of Recurrence scale score, Perceived Stress scale score, Medical Outcomes Study Social Support Questionnaire score, disease-free survival including ductal carcinoma in situ, cost, intervention acceptability, research study satisfaction, and accrual pattern of Black and younger women for the first half of patients enrolled to the study (i.e., 590 patients). All of these endpoints are hypothesis-generating, requiring additional examination in independent study.

### Analysis of accrual patterns

At 50% enrollment, a pre-planned analysis of accrual patterns will be triggered to examine site-level factors associated with accrual of a higher proportion of sub-groups of particular interest (Black and younger participants). Site-level factors of interest include sites’ volume of accrual to previous Alliance protocols, membership type, geographic region, and (for race analysis) racial composition of the neighborhood in which the site is located. Data from this analysis will be used to select Alliance sites not yet activated to the study for targeted outreach and invitation to open the study if overall enrollment is lagging, and to inform study design and site selection for future Alliance protocols seeking to enroll higher-minority samples.

### Process evaluation

The goal of the process evaluation is to explore the implementation of GETSET to inform future integration into cancer care delivery. The process evaluation includes data about cost as well as the facilitators and barriers to implementing remotely delivered medication support interventions like TMR and MI, from both the patient participant and practice staff perspectives.

*Cost analyses* are focused on ascertaining the overall cost, cost-effectiveness, and budget impact associated with delivering the TMR and MI interventions from the health system/practice (primary) and societal (secondary) perspective. Total incremental per-patient cost of MI-only, TMR-only, and TMR + MI interventions over the first 12 months, and the incremental cost of MI, TMR, and MI + TMR per 1 percentage point improvement in PDC at 12 months, compared to usual care will be reported. We are interested in estimating the total cost (sum of fixed and variable costs) in current US dollars per person recruited to the MI, TMR, or MI + TMR arms, relative to usual care. We will document all fixed and variable costs associated with delivering the interventions (above and beyond usual care) from the health system/practice perspective, including personnel costs associated with identifying eligible patients, MI counseling, TMR message delivery system setup and monitoring, and educational materials printing/mailing costs. For MI, allowable costs will include all counselor time required to schedule, complete, and document MI sessions. For TMR, allowable costs will include staff time to support the text-messaging platform, provision of phone service for 12 months to participants without text-messaging-capable phones, and staff time to troubleshoot participant problems with phones or other technical aspects of the TMR intervention. Patient time required to complete surveys and research coordinator time for study-related procedures will not be included. Cost data will be collected from a variety of sources, including administrative invoicing records and receipts (e.g., smart phones and TMR programming costs), counselor call logs in REDCap (including time spent contacting and counseling patients), and personnel time logs and wages. Cost data from all sources will be collated, deduplicated, and sorted in a spreadsheet and analyzed and reported descriptively.

*Participant process assessments* will be collected via surveys about ease of use, acceptability, responsiveness to needs, perceived benefits, and challenges associated with intervention participation. At the end of the study, participants are asked to evaluate intervention acceptability using the Acceptability of Intervention and Intervention Appropriateness Measures of Weiner et al. [47] as well as an ease-of-use questionnaire developed specifically for this study and the Alliance “Was It Worth It” questionnaire regarding the overall trial participation. Data from these patient surveys will be summarized descriptively, overall, and by race and age. Participants in the TMR component will also be asked to complete a brief survey about the ease of identifying and answering the text messages and responses, the length of time receiving text message reminders, and other feedback about the TMR components. The survey will be texted directly to participants at the same time as their monthly questions (month 9). Any participant randomized to the TMR component who receives an iPhone from The Ohio State University will be texted a brief evaluation survey at month 12 about training provided, the ease of using the iPhone, and benefits of having a smartphone.

*Practice and research staff process assessments* will be collected via key informant interviews exploring acceptability, fit with workflows, and more. Based on the process evaluation conducted in the counseling-based pilot study, we will use the Proctor Implementation Outcomes Framework to understand staff perceptions of feasibility, fidelity, acceptability, and potential sustainability [48]. We will also use the Consolidated Framework for Implementation Research (CFIR) [49] to clarify determinants of GETSET implementation. To collect these data, we will conduct semi-structured, one-on-one interviews with key informants from participating organizations, including partnering oncologists and other care team members, as well as intervention and research staff, including counselors, clinical coordinators, and technical staff. No interviews will be conducted with study participants. The qualitative interview guides will be tailored to include questions specific to each category of respondent and will address constructs such as intervention features, compatibility with needs and resources, compatibility with internal organizational structure, and process. A semi-structured interview guide can be found in Appendix XVI of the study protocol which is attached as an additional file. Data from these interviews will be transcribed in whole and analyzed thematically using CFIR-derived codebooks.

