## Methods

### Objectives

Guiding Endocrine Therapy Success through Empowerment and Technology (GETSET) is a randomized controlled trial designed to test the efficacy of two interventions compared to usual care: (1) a text messaging reminder (TMR) system and (2) telephone-based motivational interviewing (MI). Patients are randomized into one of four arms: TMR, MI, combination of TMR and MI, or enhanced usual care. The primary objective is to compare adherence to oral endocrine therapy at 12 months post-enrollment among the 4 arms. Secondary and exploratory objectives will describe (1) effects of the interventions on health-related quality of life and other patient-reported outcomes, (2) costs and cost-effectiveness of the interventions and other implementation outcomes, and (3) differences in disease-free survival across arms.

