### Study design

Target enrollment is 1180 patients. The study population will include both 30% Black women and 30% patients under age 50, which are both groups at high risk for non-adherence. An efficient study design will be used to compare each intervention and their combination to usual care, in terms of the following: ET adherence assessed by electronic pill cap (Aim 1), patient-reported outcomes including medication self-efficacy, health-related quality of life, cancer worry, knowledge and attitudes about ET (Aim 2), and relative resource use (cost) and value of interventions (cost-effectiveness) (Aim 3). We will also evaluate whether the intervention effects on outcomes differ by race and age. We used the SPIRIT reporting guidelines to ensure we have included all pertinent clinical trial protocol information in this manuscript [35] and have included the checklist as a supplement.

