### Patient selection

The trial enrolls women ages 18 + years whose initial diagnosis of stage I–III, HR + , HER2-neu negative, invasive breast cancer occurred within 18 months prior to trial enrollment. Participants must have received cancer-directed surgery and completed all other planned adjuvant therapy, except breast reconstruction. However, the extent of prior adjuvant therapy is not mandated. The trial employs a new user design, meaning that eligible patients have either initiated their first ET medication within the 6 months prior to enrollment, or have received a prescription with stated intent to initiate within 6 weeks post-enrollment, and have no medical contraindications to ET (e.g., existing, or planned pregnancy). Participants are required to use a smartphone for study participation; for participants who do not have a smartphone at baseline, phones and services are provided. Because the medication event monitoring (pill cap) system and the interventions themselves were designed to measure and address adherence to a single once-daily oral drug, patients whose ongoing therapy includes additional drugs such as a CDK 4/6 inhibitor, as well as those taking endocrine therapy on nonstandard schedules (e.g., tamoxifen 10 mg twice daily), are excluded; however, premenopausal patients treated concurrently with an injected gonadotropin-releasing hormone agonist (e.g., leuprolide) are eligible.

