### Study interventions

All study intervention components are delivered centrally by one of the coordinating centers and delivered over a 9-month period. Participants who have not started endocrine therapy medication at the time of registration must initiate the drug within 6 weeks after randomization and begin their allocated intervention within 8 weeks after randomization. Allocated intervention may be stopped prior to completion at the patient’s request or disease progression. The study schema can be found in Fig. 2.

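### All planned cost-effectiveness ratios use usual care as comparator, so none reports the cost per point of adding MI to TMR

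*Protocol article*

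**What the plan says.** The protocol article's Objectives section sets out four randomized strategies: "Patients are randomized into one of four arms: TMR, MI, combination of TMR and MI, or enhanced usual care". Under Study design, the comparator is fixed for all three aims, including cost and cost-effectiveness (Aim 3): "An efficient study design will be used to compare each intervention and their combination to usual care".

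The cost analyses under Process evaluation name two outputs. The first is "Total incremental per-patient cost of MI-only, TMR-only, and TMR + MI interventions over the first 12 months". The second is "the incremental cost of MI, TMR, and MI + TMR per 1 percentage point improvement in PDC at 12 months, compared to usual care". No ratio between two active strategies is named. Cost data are to be "analyzed and reported descriptively", and Exploratory endpoints lists cost among the hypothesis-generating endpoints.

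The Background states the purpose: the best combination of remote support strategies is not known, the trial is to evaluate which strategy is optimal, and health systems need data on resources and value before they adopt one.

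**The concern.** A health system deciding what to adopt will take one of the four strategies. If TMR turns out to be cheap and somewhat effective, the live question is whether adding MI counseling is worth its extra cost. The ratio that answers it is the extra cost of MI + TMR over TMR divided by the extra PDC gain over TMR. The planned ratio for MI + TMR divides the whole cost by the whole gain, so it credits the combination with points that TMR alone would have delivered cheaply.

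At stake is how Aim 3 is read. A combination can look like moderate value against usual care although its last and most expensive step is poor value. A strategy that costs more than another and gains no more would still appear in the table with an ordinary-looking ratio.

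**Working it through.** **Inputs from the document.** Usual care is the comparator of all three ratios (Process evaluation; Study design). The four arms are mutually exclusive (Objectives). The article states no unit cost, PDC gain or ratio, so there is no planned figure to reproduce. The 69% and 81% under Sample size are shares of patients at or above the 80% threshold, not mean PDC, and cannot serve as PDC gains.

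**Formulas.** Let C and E be the incremental cost and PDC gain against usual care, with subscript T for TMR and B for MI + TMR.

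- Planned ratio for the combination: R_B = C_B / E_B
- Ratio for TMR: R_T = C_T / E_T
- Ratio for adding MI to TMR: R_step = (C_B − C_T) / (E_B − E_T)
- Identity: R_B = (E_T / E_B) × R_T + ((E_B − E_T) / E_B) × R_step

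With E_B above E_T, R_B lies between R_T and R_step. If R_T is below R_step, R_B understates the step. If TMR were the dearer step per point, R_B would overstate it.

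**Illustration. All inputs are assumptions:** TMR costs $50, MI costs $300, the costs add to $350, and TMR gains 5 points.

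| Combined gain (points) | MI + TMR vs usual care | MI + TMR vs TMR | Factor |
|---|---|---|---|
| 6 | 350/6 = $58.3 | 300/1 = $300 | 5.1 |
| 7 | 350/7 = $50.0 | 300/2 = $150 | 3.0 |
| 8 | 350/8 = $43.8 | 300/3 = $100 | 2.3 |
| 10 | 350/10 = $35.0 | 300/5 = $60 | 1.7 |

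Check of the identity at 8 points: (5/8) × $10 + (3/8) × $100 = $6.25 + $37.50 = $43.75.

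Other assumed inputs stay within this range:

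- TMR $100, MI $300, gains 5 and 8: $50 against $100, factor 2.0.
- TMR $100, MI $200, gains 5 and 8: $37.5 against $66.7, factor 1.8.
- TMR $50, MI $500, gains 4 and 5: $110 against $500, factor 4.5.

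**Dominance.** Sample size assumes the same 81% adherence for TMR-only and MI-only. If their PDC gains were also equal (an inference, since 81% refers to the binary endpoint), the costlier single component would be dominated. With the inputs above and 5 points for MI, MI alone would still be shown at 300/5 = $60 per point against usual care, although TMR achieves the same 5 points for $50 in total.

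**The case against.** **The figure is recoverable, and other ratios are not ruled out.** Arm-level incremental costs will be reported beside the ratios, so E = C / ratio gives each gain, and the step from TMR to MI + TMR follows. In the 8-point example, 350/43.75 = 8 and (350 − 50)/(8 − 5) = $100. The article is also a condensed account and does not say that no further comparison will be made. This stands: a reader might infer that the plan hides the cost of adding MI or forbids other ratios, and the text supports neither. What remains is that the comparator is stated, not merely left open. A back-calculated step also carries no uncertainty interval.

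**The combination against MI alone.** A reader might infer that usual-care ratios make the combination look falsely better than MI alone. The illustration does not bear this out. If MI also gains 5 points, moving from MI to MI + TMR costs $50 for 1 to 5 more points, that is $50 down to $10 per point. The usual-care ratios ($58.3 down to $35 for the combination, $60 for MI) order the two correctly.

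**Phone service.** A reader might also see an error in charging TMR with "provision of phone service for 12 months to participants without text-messaging-capable phones" when "All study intervention components are delivered centrally by one of the coordinating centers and delivered over a 9-month period". The documents do not establish one. The charge covers only participants who cannot receive texts, a narrower group than in Patient selection, where "for participants who do not have a smartphone at baseline, phones and services are provided". Twelve months also matches the stated cost horizon. It is an attribution choice of small size: the 3 extra months would be about $1 to $24 per randomized TMR patient if 2% to 20% needed service at $20 to $40 a month, all assumed (0.02 × 20 × 3 = $1.2; 0.20 × 40 × 3 = $24). It forms no part of this point.

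**Low stakes.** Cost is exploratory and reported descriptively, and usual care is the comparator throughout the trial. This stands and limits the weight of the point.

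**Conclusion.** The point holds for the choice of comparator. The ratios specified do not report the quantity needed to choose among the four strategies. The ratio for MI + TMR understates the cost per point of adding MI to TMR whenever TMR is the cheaper step per point. The direction is algebraic, given that condition and a larger gain for the combination than for TMR alone.

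The size is not known. The factor of about 1.7 to 5 rests wholly on assumed costs and PDC gains and on costs that add; it is largest when the combination gains little over TMR. Whether any arm is dominated is likewise unknown until the data are in. The consequence is confined to the interpretation of an exploratory endpoint, and the primary adherence analysis is untouched.

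**What to change.** Amend the cost analyses under Process evaluation to:

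- rank the four arms by cost;
- flag arms that are dominated or extendedly dominated;
- report sequential incremental ratios among the remaining arms, and in particular the ratio for moving from the cheaper single component to MI + TMR;
- give bootstrap uncertainty for these ratios;
- keep the ratios against usual care as supplementary results.

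This costs a change of wording and a little programming on data already collected. It needs no new data, no extra patients and no change to the primary analysis.
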